#### Participants

Older individuals will be recruited via a volunteer database of the university, posters in supermarkets and other communal locations, advertisements in online and offline media, and commercial volunteer databases. An overview of the recruitment process can be found in Fig. 2. Participants will be considered eligible if they are aged 65 years or older, community-dwelling, exhibit a BMI between 23 and 32 kg/m^2^, and if their habitual diet contains animal-based food products (i.e. dairy, meat or fish) at least 5 days per week. The exclusion criteria include (1) following a self-reported vegetarian or vegan diet during the six months prior to the study, (2) following a prescribed high (≥ 1.2 g per kilogram per day (g/kg/d)) or low protein diet (< 0.8 g/kg/d), and/or or taking protein supplements on medical advice during the month prior to the study, (3) participating in a structured progressive RE training program the during three months prior to the study, (4) having experienced ≥ 4 kg of body mass loss during three months before the start of the study, (5) being diagnosed with diabetes mellitus, severe renal disease (glomerular filtration rate < 30 ml/min), neurological or neuromuscular disorders, serious cardiovascular diseases, cancer (with the exception of the following types of skin cancer: basal cell carcinoma, squamous cell carcinoma), (very) severe chronic obstructive lung disease (COPD; GOLD stage III or IV) or bowel disease, (6) chronic use of medication that affects muscle function, (7) the use of anticoagulants incompatible for muscle biopsies, (8) having a contra-indication to MRI scanning, (9) having a hip transplant, (10) participating in another research trial during the month prior to the start of the study, 11) not having a general physician.

**Fig. 2 Fig2:**
[figure not shown]
Flowchart of the recruitment process. MRI, magnetic resonance imaging; RE, resistance exercise; BMI, body mass index

#### Screening

All volunteers will receive detailed written information about the study prior to screening. Additionally, all participants will be informed via a presentation or via telephone prior to screening during which all study procedures will be explained in detail. If still interested, and after providing written informed consent, volunteers will be asked to fill out a questionnaire regarding their demographic information, lifestyle factors and medical history, and a questionnaire regarding MRI contra-indications. The medical history of the volunteers will be checked by the research physician. Additionally, body mass (kg) and height (m) will be measured using a calibrated digital scale and a wall-mounted stadiometer. Participants will be included in the study if they meet all inclusion criteria.

#### Randomization

Following inclusion, participants will be randomized to one of the three study arms on a 1:1:1 ratio, using block randomization with variable block sizes of 3, 6 and 9 to ensure equal allocation to each group. Randomization will be stratified for gender and partners will be randomized together. The randomization will be performed in Castor EDC by a member of the research team [31]. Considering the logistics of the study procedures, both the members of the research team and the participants will be aware of the group allocation.

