#### Sample size calculation

The sample size calculation was based on the primary outcome and was performed in GPower version 3.1.9.4 (Düsseldorf, Germany). Since the current study aims to compare the effect of a vegan diet to an omnivorous diet on thigh muscle volume, and to compare the effect of a vegan diet to a vegan diet in combination with RE on thigh muscle volume (two different contrasts), the sample size calculation was based on testing change in thigh muscle volume between two group comparisons. A separate two-tailed α-level of 0.05 was used for each contrast. A mean change of 4% in thigh muscle volume was expected in the vegan group. The latter was based on previous studies that assessed changes in thigh muscle volume during caloric restriction in middle aged to older adults, as no study has previously assessed the effect of a vegan diet on thigh muscle volume. Reductions in thigh muscle volume of ~ 6.5% were previously observed following a year of caloric restriction [27, 28]. Others additionally observed that the largest decline in thigh muscle volume presented itself during the first three months of caloric restriction [29]. Additionally assuming an expected reduction in the consumption of protein with a concurrent reduction in protein quality [10, 30], a mean change of 4% in thigh muscle volume was expected on the vegan diet in the present study. Using an expected mean change of 4% and standard deviation of 5% [10, 27–30], and 80% power, a total of 60 participants, 20 per group, will need to be included in the study. Considering a drop-out rate of 20%, 24 participants per group will be recruited, leading to a total of 72 participants.

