### Statistical analysis plan

All data will be treated according to the General Data Protection Regulation Act (EU GDPR) and will be collected using Castor EDC [31]. Analyses will be performed in R version 4.1.0. Prior to the analysis, group allocation will be blinded to the members of the research team that will perform the statistical analysis. Descriptive statistics will be used to explore and present baseline characteristics of the study population. Continuous data will be presented quantitatively as means and their 95% confidence intervals or, when not normally distributed, as median [interquartile range]. Categorical data will be presented as counts and percentages. Data will be analysed according to the intention-to-treat principle.

Independent samples t-tests will be performed to analyse the difference in change of thigh muscle volume and the difference in mixed MPS between groups VEG and OMNI and between groups VEG and VEG-RE. Data will be checked for normality using QQ-plots. Missing data may be imputed via multiple imputation or the related data may be eliminated. In case of a non-normal distribution, non-parametric tests will be used or data will be log-transformed. Furthermore, linear mixed models will be used to assess the differences between these groups for the other outcome measures. Participants will be added to the model as random factors. Treatment and timepoint will be added as fixed factors as main effects and their interaction. A maximum of three potential confounding factors may be added to each model as fixed factor. Model assumptions will be checked using QQ-plots and scatterplots. A two-sided p-value < 0.05 will be considered statistically significant. The Benjamini-Hochberg correction will be applied to adjust for multiple testing. In case more than two time points are tested and a significant treatment*time interaction is observed, a post-hoc analysis for will be performed using a Bonferroni correction.

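### Partners are allocated to an arm together, but the primary t-test and the participant-only mixed models treat them as independent; if couples enrol and their changes are positively correlated, type I error exceeds 5%

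*Protocol article*

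**What the plan says.** The protocol article, Randomization, describes participants being "randomized to one of the three study arms on a 1:1:1 ratio, using block randomization with variable block sizes of 3, 6 and 9", and adds: "Randomization will be stratified for gender and partners will be randomized together". Two partners who both enrol therefore share one allocation.

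The Statistical analysis plan section names the primary test: "Independent samples t-tests will be performed to analyse the difference in change of thigh muscle volume and the difference in mixed MPS between groups", for VEG against OMNI and VEG against VEG-RE. For the remaining outcomes it plans linear mixed models: "Participants will be added to the model as random factors" and "Treatment and timepoint will be added as fixed factors as main effects and their interaction". Up to three confounders may be added to those models; none is named.

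The Sample size calculation section works on individuals: "A separate two-tailed α-level of 0.05 was used for each contrast" and "Using an expected mean change of 4% and standard deviation of 5% [10, 27–30], and 80% power, a total of 60 participants, 20 per group". It applies no design effect.

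The article nowhere mentions a couple or household term, clustered standard errors, an expected number of couples or a within-couple correlation.

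**The concern.** The analysis should respect the unit of randomisation. Where two people always land in the same arm, a positive correlation between their outcomes adds to the variance of the arm mean, and a test that counts them as two independent observations misses that addition. A random effect for participant does not help: it covers repeated measures on one person, not similarity between two people.

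Positive correlation is plausible here. The diets are self-composed, and partners who live together would commonly shop and eat together. The trial's own premise is that food choice drives muscle change. The same argument applies, probably more strongly, to outcomes closer to diet, such as nutrient intake, metabolic profile and micronutrient status.

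At stake are confidence intervals that are too narrow and p-values that are too small for both primary contrasts and for the secondary outcomes.

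**Working it through.** **The plan's own figure.** The stated inputs are a change of 4%, SD 5% (standardised difference 4/5 = 0.8), two-tailed alpha 0.05, 80% power and 20 per group, with no design effect. A two-sided t-test on these inputs needs 25.5, so 26 per group; at 20 per group its power is 69.3%. A one-sided test gives 20.03. The stated 20 is thus not reproduced under the stated two-tailed alpha. That is a separate matter. Here it matters only because 69%, not 80%, is the baseline for the power figures below.

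**Design effect.** Let n be the number per arm, f the share of participants enrolled with their partner, and rho the correlation between partners' changes. An arm then holds fn/2 couples, each adding 2 × rho × SD² to the variance of the arm total:

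Var(arm mean) = (SD²/n²) × (n + 2 × (fn/2) × rho) = (SD²/n) × (1 + f × rho)

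So DE = 1 + f × rho, which cannot exceed 1 + rho because clusters have at most two members.

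**Type I error.** The planned test uses a standard error too small by a factor of √DE, so its real two-sided error is about 2 × (1 − Φ(1.96/√DE)). For f = 0.4 and rho = 0.4: DE = 1.16, √DE = 1.077, 1.96/1.077 = 1.82, error = 6.9%. The pooled t-test was also simulated at 20 per arm under no effect. Both f and rho are assumptions.

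| f | rho | DE | SE too small by (1 − 1/√DE) | Error, formula | Error, simulated |
|---|---|---|---|---|---|
| 0 | any | 1.00 | 0% | 5.0% | 5.0% |
| 0.2 | 0.2 | 1.04 | 1.9% | 5.5% | 5.5% |
| 0.3 | 0.3 | 1.09 | 4.2% | 6.0% | 6.0% |
| 0.4 | 0.4 | 1.16 | 7.2% | 6.9% | 7.0% |
| 0.6 | 0.4 | 1.24 | 10.2% | 7.8% | 7.9% |
| 0.6 | 0.6 | 1.36 | 14.3% | 9.3% | 9.5% |

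The simulation runs slightly above the formula at the larger values because clustering also lowers the expected within-arm sample variance, by the factor 1 − f × rho/(n − 1). If rho were negative the error would fall below 5%: with everyone in couples and rho = −0.1 it is about 4.0%.

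**An effect in the other direction.** Gender is a stratification factor but is absent from the t-test. If change differs by gender, that omission makes the test conservative. Simulated error with equal numbers of men and women per arm and all couples mixed-sex:

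| f | rho | No gender difference | 0.5 SD | 0.75 SD |
|---|---|---|---|---|
| 0.2 | 0.2 | 5.4% | 4.7% | 3.9% |
| 0.5 | 0.3 | 6.7% | 6.0% | 5.2% |

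**Power of a correctly computed test.** With effective n = 20/DE and a standardised difference of 0.8, power moves from 69.3% to 67.5% (DE 1.04), 65.4% (DE 1.09), 62.5% (DE 1.16) and 59.5% (DE 1.24). Only the drop from 69.3% belongs to this point.

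**The case against.** The strongest reply is that the inflation is conditional and may be trivial. It needs enrolled couples and a positive correlation between partners in the *change* of the outcome, and the article gives neither. Recruitment is aimed at individuals, and both partners would have to meet the age, BMI, MRI and medical criteria, so a low share of couples is at least as plausible as a high one. At 20% in couples and a correlation of 0.2 the excess is half a percentage point, and a gender difference in change could cancel it. The mechanism is also partly inferred: the article says that each participant selects products individually and that all participants attend nutrition meetings, so neither is peculiar to couples. All of this stands. It limits the size and certainty of the consequence; it does not reconcile the analysis with the allocation. The gender offset is accidental and would vanish once gender is adjusted for.

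It might also be said that a journal article leaves such detail to a fuller document. That does not answer the point, because the article names the primary test, and that test assumes independence.

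Two stronger readings are tempting and are not supported. A reader might infer that type I error definitely exceeds 5%; without a couple count and a correlation, this cannot be stated as fact. A reader might also infer that mixed-gender couples break the gender-stratified blocks. The article does not say how couples are entered in the randomisation system, and such operational detail is commonly left to the full protocol.

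**Conclusion.** The stated analysis does not match the stated randomisation. That much is on the face of the document and rests on no assumption. The consequence is conditional: if couples enrol and partners' changes are positively correlated, standard errors are too small and the nominal 5% test rejects too often. Over the assumed range the real error runs from about 5.5% to 9.5%. It remains at 5% with no couples or no correlation, and it may be lower where gender differences in change make the unadjusted test conservative.

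This should be fixed, but it does not on its own invalidate the trial. Confidence is high that couples are ignored in the analysis and medium on how much that matters.

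**What to change.** - Record a couple identifier, treating each single participant as a cluster of one.
- Analyse change in thigh muscle volume and mixed MPS with gender as a covariate and one of two pre-specified devices: a random couple intercept with Kenward-Roger or Satterthwaite degrees of freedom, or couple-clustered standard errors with a small-sample correction. The second is preferable if couples are few, because the couple variance may be estimated as zero and the model then reverts to one that ignores couples. With two couples per arm and a correlation of 0.2, a simulation gave this in about 35% of trials.
- In the other mixed models, nest participant within couple.
- Report the number of couples per arm.

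The cost is one extra variable, one extra model term and a small loss of nominal precision. No new outcome measurement is needed. If few couples enrol, little changes; if many do, the primary inference is protected.

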### Intervention

#### Study diets

All participants will attend monthly nutrition information meetings, commencing in the week prior to the initiation of the study diets. The content presented during these meetings will be based on the Dutch national dietary guidelines [32]. The participants assigned to the VEG and VEG-RE groups will be instructed to abstain from consuming any animal-based food products throughout the intervention period. During the nutrition information meetings, these groups will be informed regarding suitable plant-based replacements for animal-based food products, such as legumes, nuts, and dairy alternatives. Furthermore, these participants will receive guidance regarding the adoption of a vegan diet and will be given the opportunity to address any inquiries or concerns pertaining to the intervention. During these meetings, additional emphasis will be laid on the nutrients protein, cobalamin, vitamin D and calcium. The participants will be equipped with practical resources, including recipes and pocket-size hand-outs containing information regarding, for example, (non)vegan ingredients and vegan product logos.

With respect to the participants assigned to the control (OMNI) group, their habitual dietary intake as omnivores will form the basis for their dietary consumption throughout the intervention period. To address the possibility of potential confounding effects arising solely from increased adherence to the Dutch national dietary guidelines within the vegan groups, the control group will also participate in monthly nutrition information meetings. During these sessions, information about the Dutch national dietary guidelines [32] will be disseminated, including the recommendations regarding the consumption of animal-based food products. The control group will, however, not be strictly instructed to comply with these guidelines.

All participants will be provided with commercially available food products on a bi-weekly basis. Participants can select these products from a predefined list and the provided products will thus vary among participants. The participants in the vegan group will choose from a range of plant-based food products including legumes, nuts, vegetables, and plant-based analogues for dairy or meat, among others. On the other hand, the control group will choose from a predefined list containing only animal-based food products such as meat, dairy, and poultry. By providing these products we aim to assist participants in effectively implementing their assigned diet and to promote adherence across all groups. All participants will further be instructed to discontinue the use of any nutritional supplements one week prior to the intervention, except for those supplements that are medically prescribed and vitamin D supplements, as daily vitamin D supplementation is recommended by the Dutch Ministry of Health for older adults [33]. Participants who were not already taking vitamin D will be advised, but not instructed, to supplement either 10 µg (participants aged < 70) or 20 µg (participants aged ≥ 70) of vitamin D per day. The use of vitamin D supplementation will be recorded.

#### Resistance exercise

Participants assigned to the VEG-RE group will engage in progressive RE twice a week throughout the intervention period. The exercise sessions will be conducted at a separate training facility located in Wageningen. The training protocol employed in this study is based on a pre-existing RE protocol utilized in previous research conducted by our research group [34]. The exercise sessions will have a duration of approximately one hour and will be supervised by an experienced trainer. 

Initially, participants will be introduced to the proper techniques and correct execution of the exercises. Subsequently, sub-maximal strength (8-repetition maximum, 8-RM) of the lower-extremity exercises will be measured to determine the appropriate training load for the exercise protocol. The 8-RM of the lower extremity exercises will be assessed at least every 6 weeks starting at the first training session, and the exercise intensity will be adjusted accordingly. Sub-maximal strength (15-RM) of the upper-extremity exercises will be estimated at the second training session. Each training session will start with a 5-minute warm-up through light exercises. Subsequently, the following exercises will be performed in varying order (1) Leg Press (Body Solid, G9S system, Illinois, USA), (2) Leg Extension (Body Solid, G9S system, Illinois, USA), (3) Lat Pulldown (Body Solid, G9S system, Illinois, USA), (4) Chest Press (Body Solid, G9S system, Illinois, USA), (5) Dumbbell Shoulder Press, and (6) Cable Row (Body Solid, G9S system, Illinois, USA). Due to logistic aspects of the study, participants may perform a Push Up and a Dumbbell Pullover instead of the Chest Press and Lat Pulldown at two of the 24 training occasions during the study. Four sets of 10 to 15 repetitions will be performed for the exercises of the lower extremity, with the intensity ranging from 50% of their estimated 1-RM in week 1 to 75% in week 12. Furthermore, three sets of 15 repetitions will be performed for the upper body exercises, ranging from 50% of their estimated 1-RM in week 1 to 60% in week 12. Finally, all exercise sessions will be concluded with a 5-minute cool-down through light exercises. The experienced trainer will monitor the participants’ progress and well-being regularly.

#### Deuterated water protocol

To determine mixed MPS rates, expressed as daily protein fractional synthesis rates (FSR, %/day), participants will be instructed to follow a deuterated water (D_2_O; or deuterium oxide; purchased from Cambridge Isotope Laboratories and Sigma Aldrich) supplementation protocol for eleven days. The dosing protocol that will be utilized in this study has been previously described elsewhere [35]. The dosing protocol will consist of one dosing day and ten maintenance days. The protocol will be initiated one day prior to the start of the dietary intervention. On this first day, the dosing day, participants will orally consume two doses of 100 mL of 70% enriched D_2_O, with four hours in between the doses. Over the subsequent 10 days, participants will be instructed to consume 20 mL of D_2_O daily to ensure a steady-state body water deuterium enrichment over this period.

#### Compliance

To monitor compliance during the intervention, participants will be provided with a logbook. Participants will be instructed to document any deviations from the study protocol and report any complications related to the dietary changes as well as issues unrelated to the intervention. The logbooks will be reviewed by the research team during each test day, and any issues or concerns identified will be discussed with the participants. Attendance to the RE sessions and nutrition information meetings will be logged. Additionally, the dietary intake of all participant groups will be evaluated at baseline, at the beginning of the intervention, during week 6, and again during week 12 of the intervention, allowing us to assess compliance to the diets after data collection. No feedback will be provided to the participants regarding their dietary intake during the intervention period. Participants will be instructed not to change their habitual physical activity levels during the study, with the exception of the discontinuation of RE. To assess whether compliance to this rule is successful, physical activity will be evaluated at baseline, at the beginning of the intervention and during the last month of the intervention. The procedures are described in more detail in the study outcome section.

### Study outcomes

#### Thigh muscle volume and fat distribution

An overview of all study outcomes is presented in (Table 2). The primary outcome thigh muscle volume (L), and secondary outcomes thigh muscle fat infiltration (MFI; %), liver fat fraction (LFF; %), visceral adipose tissue (VAT; L) and abdominal subcutaneous adipose tissue (ASAT; L), will be assessed using a neck to knee MRI scan (Philips Ingenia Elition 3 T X, Philips Healthcare, Best, the Netherlands) at baseline and after 12 weeks. T1-weighted transverse images will be obtained using a dual-echo FFE scan sequence for the quantification of thigh muscle volume, MFI, VAT, ASAT, and LFF. Participants will enter the scanner head-first. Parameters for the thighs will be: Repetition time (TR), shortest; echo times (TE), shortest; flip angle, 10⁰. Parameters for the abdomen will be: TR, shortest; TE, shortest, 1 ms; flip angle, 10⁰. Image resolution for the scans covering the thighs is 1.84 × 1.84 × 4 mm, and for the scans covering the abdomen is 3 × 3 × 6 mm.

**Table 2 Tab2:** Overview of the outcome measures

Outcome	Method			Time			
		Screening	Baseline	Day 10		Week 6	Week 12
Primary							
Thigh muscle volume	MRI-scan		X				X
Secondary							
Thigh muscle fat infiltration	MRI-scan		X				X
Fat distribution	MRI-scan; DEXA-scan		X				X
Muscle strength	Biodex		X				X
Mixed muscle FSR	Muscle biopsy		X	X			
	Blood sample		X	X			
	Saliva sample		Daily for 11 days				
Bone mineral density; lean mass	DEXA-scan		X				X
Bone turnover markers	Blood sample		X			X	X
Metabolic profile	Blood sample		X			X	X
Blood pressure	Blood pressure monitor		X			X	X
Micronutrient status	Blood sample		X				X
hs-CRP	Blood sample		X				X
GI health	Stool sample*		X				X
	Blood sample*		X				X
	GSRS		X			X	X
Body mass	Scale	X	X	X		X	X
Dietary intake	Food diary		X	X		X	X
Other							
Participant characteristics	Questionnaire	X					
Height	Stadiometer	X					
WOMAC-index**	Questionnaire		X				X
DNA methylation	Blood sample		X				X
Handgrip strength	Hand dynamometer		X				
Physical activity levels	Accelerometery		Daily for 17 days				Daily for 7 days***
	Activity diary		Daily for 17 days				Daily for 7 days ***
Compliance	Attendance nutrition information meetings	Monthly at each information meeting					
	Attendance RE	Twice a week at each RE session					
	Food diary		X		X	X	X
	Accelerometry		Daily for 17 days				Daily for 7 days***

Abbreviations: *MRI* Magnetic resonance imaging, *DEXA* Dual X-ray Absorptiometry, *GI* Gastro-intestinal, *HS-CRP* High-sensitive C-reactive protein, *GSRS* Gastro-intestinal symptom rating scale, *RE* Resistance exercise, *WOMAC* Western Ontario and McMaster Universities Osteoarthritis Index

^*^Not in the group that is allocated to participate in a resistance exercise program. ^**^only in participants with self-reported (osteo)arthritis at the moment of screening; ^***^ accelerometery may be performed anytime during the last month of the intervention. To be placed on page 23, after the section ‘Other study outcomes’.

Upon arrival after a two hour fast, participants will complete the MRI eligibility form again. Subsequently, participants will change into MRI suitable clothing and will be provided with earplugs and headphones to reduce the scanner noise. A surface coil will be placed on the participants to allow for the measurement of LFF. Communication with the participants will be via the intercom. The participants will be instructed to hold their breath on expiration when the stacks covering the abdomen are obtained to reduce respiratory motion artefacts. The total scanning time for each session will be approximately 13 min. The obtained MRI images will be analyzed using AMRA^®^ Researcher (AMRA Medical, Linköping Sweden), as previously described in detail [36].

